## Abstract

**Simple Summary:**

Active breaks have led to improvements in physical fitness, daily steps taken or even improvements in the health of participants who have taken them. However, no study has assessed how they affect physical literacy (PL). This study will try to explore the effect of a programme based on active breaks (PLBreaks) on PL and body composition of schoolchildren. For this purpose, the PLBreaks programme will be carried out for 3 months and 3 days a week. The PLBreaks programme will consist of two blocks of 10 min of different physical activities (PA). The first block will be focused on the acquisition of knowledge and healthy life habits that will contribute to the development of the domains of knowledge and understanding and daily activities. The second block will be focused on the physical competence and motivation through games. Furthermore, a control group who will follow their usual daily activities is included. This would allow the investigation of whether the PLBreaks programme leads to an improvement in PL and body composition in schoolchildren. If the effectiveness of the programme is demonstrated, the programme could be included in public education programmes, representing a scientific advance in terms of improving health-related PA and adherence, as well as the prevention of diseases associated with inactivity.

**Abstract:**

(1) Background: Several studies have shown that active breaks have led to different improvements in their participants. However, no studies have assessed how they affect physical literacy (PL). (2) Aims: Therefore, this study will examine the effect of the PLBreaks programme on school children’s PL and body composition. (3) Methods: A parallel-group randomised controlled trial will be conducted with assessments of PL (Canadian Assessment of Physical Literacy Development) and body composition (height, bodyweight, fat mass and fat-free mass) before and after an active breaks programme. PLBreak programme will run for 3 months and will be carried out 3 days a week for 20 min each day. The PLBreaks programme will consist of two blocks of 10 min of different physical activities (PA). The first block will be focused on the acquisition of knowledge and healthy life habits that will contribute to the development of the domains of knowledge and understanding and daily activity. The second block will be focused on physical competence and motivation throughout games. (4) Conclusions: The present study will investigate the efficacy of PLBreaks in schoolchildren in improving their PL and body composition. If the efficacy of the program is demonstrated, including the programme in public education programmes can be possible. This could be a scientific breakthrough in terms of health-related PA improvement and adherence, as well as the prevention of diseases associated with inactivity.

## 1. Introduction

The World Health Organisation (WHO) defines overweight and obesity as chronic diseases characterised by abnormal or an excessive accumulation of body fat that can be harmful and represent a health risk. Childhood obesity has increased in the last 40 years, making it one of the major problems and challenges for public health in advanced societies [1,2,3]. Focusing on Portuguese population, previous studies showed that the prevalence of overweight in children and adolescents ranges between 20% and 40%, and obesity between 10% and 15% [4]. Likewise, the Childhood Obesity Surveillance Initiative (COSI) report for Portugal in 2019 showed a reverse trend in the prevalence of overweight (from 37.9% to 29.6%) and obesity (from 15.3% to 12.0%) in children aged 6 to 8 years-old [5]. However, data are still worrying, as the National Food, Nutrition and Physical Activity survey 2015–2016 (IAN- AF, 2015–2016) informed that the prevalence of overweight and obesity was 25% in children, and even higher in adolescents, reaching 32.3% [6]. 

Multiple factors influence the development of overweight and obesity, such as genetic, neuroendocrine, energy expenditure-related and environmental factors [7]. Specifically, one of the major problems in current society is the high level of sedentary lifestyles, which is considered the disease of the 21st century [8,9]. In Portugal, IAN-AF, 2015–2016 [6] published that only the 57.5% of children and adolescents (aged 6–14 years) met WHO recommendations (60 min/day of moderate/vigorous physical activity; i.e., ≥3 METS/hour), and this compliance is higher in children versus adolescents (68.3% versus 57.1%). 

Hence, due to the numerous problems that physical inactivity can lead to and the risks it poses to health in both the short and long terms, it is a challenging problem for society. The health benefits of physical activity (PA) and its importance in disease prevention have already been demonstrated [10]. Moreover, it is estimated that physical fitness is one of the most relevant markers of health [11] as well as a significant predictor of cardiovascular disease mortality and morbidity [12,13,14,15]. Although genetic inheritance determines part of the individual’s physical fitness, it is also influenced by environmental factors and lifestyles. This is where physical exercise became relevant [11], as numerous studies have reported benefits in terms of body composition after a PA intervention [16,17]; thus, prevention at this age could be essential for avoiding an increase in health risks.

Physical literacy (PL) can play a relevant role in enhancing physical fitness since it can influence the practice of physical activity. PL was defined in the Bulletin of the International Council of Sport Science and Physical Education of the United Nations Educational, Scientific and Cultural Organization as the motivation, confidence, physical competence, knowledge and understanding to value and participate in a physically active lifestyle [18]. Similarly to how reading, writing, listening and speaking are combined to formulate linguistic literacy, PL is a progressive journey in which the different components interact holistically to facilitate a life of participation and enjoyment of PA.

The positioning of PL as a determinant of health is not a novel idea, but little focus has been placed on what it means and its implications. Few studies have investigated the association between PL and health, but it has already been shown to be related to body composition [19], physical fitness, blood pressure and HRQoL [20]. Active breaks may be highly relevant for the acquisition of PA benefits. Previous studies have shown that active breaks based on educational and health interventions have led to improvements in participants’ fitness and health [21,22], self-efficacy [23], quality of life and self-confidence [24].

In Portugal, only one study [25] related to PL has been found, which aimed to validate a battery for its evaluation. However, this battery was focused on adolescents aged between 15 and 18 years; thus, there are currently no studies that evaluated PL in children and no studies that have developed programmes aimed at improving PL. Despite this, we consider this multidimensional assessment and intervention model to be of great interest. 

Thus, this study aimed to (1) evaluate the effectiveness of the Physical Literacy Breaks (PLBreaks) programme on schoolchildren’s PL (general PA, physical competence, motivation and knowledge domains) and (2) evaluate the effectiveness of the PLBreaks on children’s body composition.

## 2. Materials and Methods

### 2.1. Design

A parallel-group randomised controlled trial will be conducted including a 3-month intervention phase, followed by 1-month follow-up. Participants will be randomly assigned to the experimental or control group. For both groups (control and experimental), assessments will be carried out at baseline (before starting the intervention), right after finishing the intervention and an additional follow-up assessment 1 month after the end of the programme. The study will be conducted following the *Consolidated Standards of Reporting Trials Statement* (CONSORT) [26].

### 2.2. Ethics

The Ethics Committee of the University of Evora approved this project (approval number: 22047) according to the updates of the Declaration of Helsinki and modified by the 64th General Assembly of the World Medical Association (Fortaleza, Brazil, 2013) and the Law 14/2007 on Biomedical Research. The study has been registered in the Australian New Zealand Clinical Trials Registry (Registration Number: ACTRN12622000562774; https://www.anzctr.org.au/ (accessed on 22 May 2022)).

### 2.3. Sample Size

Sample size computations were conducted by using G*Power software 3.1.9.4 (Kiel University, Kiel, Germany) and selecting the statistical test to compare the difference between two independent means (two groups). Thus, accepting a 0.05 alpha risk and a 0.2 beta risk in a bilateral contrast and assuming a moderate effect size of 0.5 [27], a total of 128 participants (64 subjects in the experimental group and 64 in the control group) were sufficient for achieving a minimum power of 80%. 

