### 2.6. Intervention

Experimental group: A 3-month physical active breaks intervention will be carried out in the educational centres during break times, with a frequency of three times per week. The duration of each session will be between 20 min, based on the time pre-established by each educational centre for the students’ break.

Specifically, in order to develop the domains that make up physical literacy, the PLBreaks programme will consist of two blocks of 10 min. Both blocks will favour the development of physical competence through different physical activities. In addition, the first block will be focused on the acquisition of knowledge and healthy life habits that will contribute to the development of the domains of knowledge and understanding and daily activity. Finally, the second block, in addition to favouring physical competence, will try to improve motivation through different strategies that will be detailed below. 

In the first block, activities will be carried out to develop the knowledge and understanding of concepts and attitudes related to physical activity (Figure 1). This will be performed with the following activities:Find the question: Participants, in pairs, will have a map with different points marked on it (beacons). They will have to find the maximum number of beacons and answer the questions that are exposed in these points on a record sheet.Body performances: Participants in groups will have to act out the content of the week through body movements and their partners will have to guess their actions. Card relay race: Participants will be divided into teams, which will be placed in rows. Each participant of each team will have to run individually to a table located about 30 metres away, and once there, they will find a series of cards, and will have to place the card they will be holding on their corresponding (partner) and return to the end of the line for the next participant to come out. 

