The second block will be based on active play, as it is fundamental in the transmission of values and attitudinal content as well as stimulating social and civic relations with others [29]. Similarly to previous studies [30,31], for this study, the proposed Ontario Physical and Health Education Association’s PlaySport activities (http://www.playsport.net/ (accessed on 20 May 2022)) will be used (Figure 1). During the games, basic skills will be developed, such as moving, jumping, spinning or throwing, thus trying to improve them as well as the children’s motivation. The games will have a cooperative and competitive component due to the motivational benefits this can bring [32]. The activities will be adapted to the initial level of the children’s.

Specifically, during the second block, in order to improve the motivation and confidence of the participants, some strategies should be fulfilled. In this regard, participants’ inclusion will be ensured during all activities (both by gender and ability) by adapting all activities so that all participants can learn and participate actively. Furthermore, to satisfy the need for peer relationships, strategies will be used in group formation and cooperative activities with a common goal that participants will have to achieve together. [33]. In addition, activity coordinators and children will be encouraged to provide verbal feedback to participants in order to ensure active participations, fostering relation-inferred self-efficacy (RISE) [30,34]. Finally, they will be provided time at the end of each session to express their opinions [33].

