### 2.8. Statistical Analysis

Descriptive statistics and computations will be performed with SPSS (version 25.0; IBM SPSS Inc., Armonk, IL, USA). Data will be presented as means and standard deviation (SD).

The normality and homogeneity of data will be checked applying Kolmogorov–Smirnov and Levene’s test, respectively. Then, a repeated measures ANCOVA will be applied to analyse the intervention effects on the different dependent variables, adjusted by age and baseline outcomes. Cohen’s d (with 95% confidence interval) will be also included in the results as the effect size. Effect sizes thresholds will be interpreted as follow: >0.2, small; >0.5, moderate; >0.8, large [27]. Statistical significance will be computed for the effect of time and the interaction group × time. Alpha level will be fixed at *p* ≤ 0.05.

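### The experimental arm is treated in shared group sessions, but the sample size and the ANCOVA treat all 128 children as independent

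*Protocol article*

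**What the plan says.** **Sample size (2.3).** The calculation is made by "selecting the statistical test to compare the difference between two independent means (two groups"), "accepting a 0.05 alpha risk and a 0.2 beta risk in a bilateral contrast" and "assuming a moderate effect size of 0.5". The result is 128 children, "64 subjects in the experimental group and 64 in the control group", which the article says "were sufficient for achieving a minimum power of 80" percent. No ICC, design effect or group size enters.

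**Allocation (2.4).** Children are randomised individually, 1:1.

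**Delivery (2.6).** "A 3-month physical active breaks intervention will be carried out in the educational centres during break times", three times a week. The first block uses pairs, groups and relay teams. In the second, "strategies will be used in group formation and cooperative activities with a common goal that participants will have to achieve together", and both coordinators and children are encouraged to give verbal feedback. Control children keep their usual break, in which they mix and play freely with peers.

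**Analysis (2.8).** "a repeated measures ANCOVA will be applied to analyse the intervention effects on the different dependent variables", with age and the baseline value as the only adjustment. Neither session group nor school appears as a term.

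**The concern.** Children who share sessions, coordinators and team-mates for three months may end up more alike than children who do not. Here that is partly intended: the second block relies on peer interaction and feedback to raise motivation and confidence, which is one of the four CAPL-2 outcome domains in section 2.7. The grouping arises after randomisation and, as organised treatment, only in the experimental arm. The design is therefore partially nested.

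The repeated measures structure handles correlation within a child over time. It does not handle correlation between children in the same session group. If that correlation is positive, confidence intervals are too narrow and the test rejects too often, and the 80% in section 2.3 does not describe the design that will be run. The conclusions of the article offer the programme for use in public education if it proves efficacious, so control of false positives on the group comparison matters.

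**Working it through.** **Inputs from section 2.3:** two-sided alpha 0.05, standardised effect d = 0.5 (so SD = 1), 64 per arm.

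**Assumed, because the article gives none:** session-group size m, ICC ρ, stable group membership, k = 64/m groups, and controls independent of one another.

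**Step 1: reproduce the stated figure.** With 126 degrees of freedom and noncentrality 0.5 × √(64/2) = 2.828, the exact two-sample t-test has power 80.15%. At 63 per arm it is 79.5%. The arithmetic in 2.3 is right under independence and has almost no reserve. The normal approximation used in step 2 gives 80.7% at 64 per arm, which is the like-for-like reference there.

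**Step 2: inflate the experimental arm only.**

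- Design effect: DE = 1 + (m − 1)ρ
- True SE = √[(DE + 1)/64]; naive SE = √(2/64) = 0.1768
- Power = Φ(0.5/SE − 1.96)
- Type I error of the naive test = 2 × [1 − Φ(1.96 × naive SE / true SE)]

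| m | ρ | DE | Effective n (64/DE) | True SE | SE ratio | Power | Type I error |
|---|---|---|---|---|---|---|---|
| 10 | 0.01 | 1.09 | 58.7 | 0.1807 | 1.02 | 79% | 5.5% |
| 16 | 0.05 | 1.75 | 36.6 | 0.2073 | 1.17 | 67% | 9.5% |
| 21 | 0.10 | 3.00 | 21.3 | 0.2500 | 1.41 | 52% | 17% |

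For the middle row, 0.5/0.2073 = 2.412, and Φ(2.412 − 1.96) = 67%.

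**Step 3: check by simulation.** This used four schools with 16 children per arm in each, a naive t-test and 20,000 trials.

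- Session-group effect in the experimental arm only: type I error 9.4% at ICC 0.05 and 14.3% at ICC 0.10.
- School effect common to both arms, ICC 0.10, no session-group effect: 4.2%.
- School effect 0.10 plus session-group effect 0.05: 8.8%.

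The inflation comes from the session group, not from the school.

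**Step 4: degrees of freedom.** A valid analysis must also allow for the small number of groups. The Satterthwaite form is df = (DE + 1)² / [DE²/(k − 1) + 1/63]. For m = 16, ρ = 0.05: 2.75² / (1.75²/3 + 1/63) = 7.3, critical value 2.35, and unadjusted power about 55%. The other two rows give df 18.5 and 3.6, with power about 75% and 32%.

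**Step 5: baseline adjustment**, which 2.8 uses and 2.3 does not count. For m = 16, ρ = 0.05 and an assumed baseline correlation r, the variance of the difference is (1 − r²)(DE + 1)/64 if ρ is defined after adjustment, or [2(1 − r²) + (m − 1)ρ]/64 if before. By the normal approximation, without the loss in step 4, power is 76% to 80% at r = 0.5 and 85% to 92% at r = 0.7. The error rate is not repaired: under the first definition the SE ratio is unchanged, so it stays at 9.5%. Under the second, a simulated ANCOVA at r = 0.5 gave 11.2%, because adjustment shrinks the residual variance but not the group component.

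**The case against.** **The size is unknown.** The article gives no ICC, session size or number of centres, and does not say that group membership stays fixed for three months. At the low end of the range the effect is negligible. This stands: understated standard errors and excess type I error are conditional on a positive session-group correlation, and the figures are assumptions.

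**Individual randomisation protects the comparison.** For school effects it does. A reader might infer that recruiting from several centres makes this a cluster trial and apply a design effect to both arms. The documents do not support that: allocation is by child, and ignoring a school effect shared by both arms left the naive test slightly conservative (4.2%) when each school held both arms equally. But randomisation cannot remove correlation created afterwards by shared sessions.

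**Controls also interact.** Section 2.6 says so. Treating them as singletons is a modelling assumption, not something the protocol states. It is reasonable because their breaks are not organised into treatment groups.

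**Baseline adjustment may restore the power.** It may (step 5), so a reader should not infer that the adjusted analysis must fall short of 80%. It does not restore the error rate.

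**An article condenses.** Session sizes and random-effects details often sit in the full protocol or analysis plan, and their absence is not the point here. Section 2.3 asserts a minimum power from an independence calculation, and section 2.8 names the model and its covariates. Both are stated choices that do not fit the delivery in 2.6.

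**Conclusion.** The point holds in conditional form. The stated power and the named model ignore session-group correlation in the experimental arm. If that correlation is positive, the SE is understated by a factor of about 1.02 to 1.41 over the assumed range. Type I error is then 5.5% to 17%, and the protocol's own unadjusted power is 79% to 52%, or about 75% to 32% with Satterthwaite degrees of freedom. Because the exact figure is only 80.15%, even a small positive ICC takes it below 80%. These values rest on assumed ICCs and group sizes, stable groups and independent controls.

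Two stronger readings should be set aside. The sample size is not miscalculated, since 128 reproduces exactly under its stated assumptions. Nor can the trial be declared underpowered, or its error rate inflated, as a matter of fact, because the ICC, the group size and the baseline correlation are all unknown.

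**What to change.** 1. **Record** each experimental child's session group and every child's school from the first session. Group membership may not be recoverable later.
2. **In 2.8**, specify a partially nested mixed model: a random session-group effect in the experimental arm, school as a fixed effect, age and baseline as now, and small-sample degrees of freedom. State that controls enter as singletons and that this is a modelling assumption. If each school has only one session group, note that the session-group term cannot be separated from a school-by-treatment interaction.
3. **In 2.3**, replace the claim of at least 80% power with the power at 64 per arm over a stated range of ICC, group size and baseline correlation, using the same degrees of freedom.

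**Cost.** One recorded identifier, changed analysis wording and a restated power figure. No children are added. The price is wider confidence intervals and a stated power that may be materially lower than 80%. With about four groups, the session-group variance will also be poorly estimated, and the text should say so.

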### 2.4. Randomisation and Blinding

Participants will be randomly assigned to the experimental (PLBreaks program) or control groups. Prior to enrolling participants (1:1), the Research Randomizer software (version 4.0, Geoffrey C. Urbaniak and Scott Plous, Middletown, CT, USA; http://www.randomizer.org) [28] will be employed to create a randomisation sequence. A member of the research team, with no active clinical involvement in the trial, will conduct this process. Group assignment will be hidden in a password-protected computer file. Participants will be aware of their group assignment, but outcome assessors and data analysts will be blinded to the participants group allocation.

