### 2.5. Participants

Participants have to meet the following inclusion criteria: (1) to be aged between 8 and 16 years old; (2) to be registered and/or residing in Portugal; (3) not suffer from pathologies that contraindicate exercise practice, limit the execution of the PA programme or require special attention; (4) to be authorised by parents or legal guardians; and (5) to participate in the study.

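### Allocation is described as one 1:1 sequence with no stratification by centre, and centre is missing from the ANCOVA: a modest loss of precision and a delivery risk in small centres, not a bias

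*Protocol article*

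**What the plan says.** - **Allocation (2.4).** The unit is the child: "Participants will be randomly assigned to the experimental (PLBreaks program) or control groups". The list is made in advance ("Prior to enrolling participants (1:1), the Research Randomizer software") and is described in the singular: the software "will be employed to create a randomisation sequence". The section covers who runs the process, concealment and blinding. It mentions no strata, blocks or lists by centre.
- **Centres (2.6).** The programme "will be carried out in the educational centres during break times". The plural shows more than one centre, and session time is "based on the time pre-established by each educational centre". Neither the number of centres nor their sizes are stated.
- **Activities (2.6).** The first block uses pairs, groups and relay teams. In the second, "strategies will be used in group formation and cooperative activities with a common goal". Each centre therefore needs a workable number of experimental children.
- **Age (2.5).** Children are "to be aged between 8 and 16 years old".
- **Analysis (2.8).** The repeated measures ANCOVA is "adjusted by age and baseline outcomes". Centre is not listed.
- **Sample size (2.3).** 64 children per arm, from a two-sided 0.05 test, 80% power and a standardised difference of 0.5.

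**The concern.** Centre shapes how the programme is delivered, yet it appears neither in the allocation as described nor in the stated model. A single list can hold the 1:1 ratio over the whole trial without holding it inside any one centre.

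Two things are at stake. First, if centres differ in outcome, that variation stays in the residual and in any chance imbalance between arms, so the estimate is less precise than it could be. Second, a small centre may draw too few experimental children to run pairs and teams. A centre term cannot repair this second problem afterwards; only allocation within centre can. The lists are made before enrolment, so the choice has to be settled by then.

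**Working it through.** **Inputs from the article:** 128 children, 64 per arm, d = 0.5, two-sided alpha 0.05 (2.3); individual 1:1 allocation from one sequence (2.4); several centres (2.6); age and baseline as covariates (2.8).

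**Assumptions, because the article gives no figures:** centre size m, number of equal centres k, and the share of outcome variance lying between centres (ICC).

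**1. The plan's own sample size.** Exact power of the two-sample t test, with noncentrality d·√(n/2) and 2n − 2 degrees of freedom, is 0.795 at n = 63 and 0.801 at n = 64 per arm. The stated total of 128 is reproduced.

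**2. Split within one centre.** With an unrestricted list, the experimental count in a centre of m children is X ~ Binomial(m, 0.5). If the totals are fixed at 64:64, X is hypergeometric (128, 64, m). A 65:35 split or worse in either direction has probability 2·P(X ≥ r), where r is 0.65m rounded up.

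| m | r | Unrestricted | Fixed 64:64 |
|---|---|---|---|
| 10 | 7 | 0.34 | 0.32 |
| 20 | 13 | 0.26 | 0.22 |
| 30 | 20 | 0.10 | 0.06 |

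**3. At least one badly split centre.** 128 children in k equal centres, totals fixed at 64:64, by simulation:

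| k | Children per centre | Any centre two-thirds to one arm, or worse | Any centre 75:25 or worse |
|---|---|---|---|
| 2 | 64 | 0.0002 | about 0 |
| 3 | about 43 | 0.03 | <0.001 |
| 4 | 32 | 0.08 | 0.007 |
| 6 | about 21 | 0.55 | 0.08 |
| 8 | 16 | 0.77 | 0.37 |

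Serious imbalance is a problem of many small centres.

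**4. Enough children to run a session.** The chance of three or fewer experimental children, P(X ≤ 3), is 0.36 in a centre of 8 and 0.17 in a centre of 10. Three children cannot form two pairs.

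**5. Effect on the test.** With total SD 1, the standard error of the arm difference is √(2/64) = 0.177. The part due to chance centre imbalance has SD of about √(ICC·2/64), which is 0.04 at ICC 0.05 and 0.08 at ICC 0.20, against a target of 0.5. Simulating an unadjusted t test with centre effects (4 or 12 centres, ICC 0.05 or 0.20) gave type I error of 0.046 to 0.051 and power of 0.80 to 0.81.

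**6. Gain from stratifying and adjusting.** Removing the between-centre share turns d into 0.5/√(1 − ICC). Power at 64 per arm, against 0.801 without the change:

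| ICC | Effective d | Power |
|---|---|---|
| 0.01 | 0.503 | 0.805 |
| 0.05 | 0.513 | 0.821 |
| 0.10 | 0.527 | 0.841 |
| 0.20 | 0.559 | 0.881 |

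The degrees of freedom spent on centre hardly matter: at ICC 0.05 with 12 centres (11 fewer degrees of freedom, 115 instead of 126), power is still 0.821. These gains are upper figures, because adjustment for the baseline outcome already absorbs part of the centre variation.

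**The case against.** **Silence in a condensed article.** Section 2.4 does not say that the list is unstratified, and the full protocol may give strata and blocks. This stands for the allocation half, where the point can only be that the article describes one sequence and names no centre strata. It does not reach the analysis half, because section 2.8 gives an explicit covariate list and centre is not on it.

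**Confounding.** A reader might infer that school differences become confounded with the programme. The documents do not support that. Children are randomised individually, so any imbalance is by chance, and the test's error rate already accounts for it, as step 5 shows. Only break time is tied to the centre in the text; nothing says that test staff, facilities or testing season differ between centres.

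**Centres falling almost wholly in one arm.** This is also tempting and unsupported. It would need many small centres, which the article does not report. With two to four equal centres, a 75:25 split in any of them has a chance of at most 0.007.

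**The wide age range.** It adds little. Age is already a covariate, and splitting each centre's list by age band would create small cells and incomplete blocks that weaken the balance sought.

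**Limits of the remedy.** Allocation within centre still gives a 10-child centre only about five experimental children. That is true, but it removes the chance of ending up with three or fewer merely through the draw.

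**Conclusion.** The point holds as a matter of precision and delivery. As described, the plan leaves centre out of both the allocation and the model, although centre governs part of the delivery. Validity is not threatened: the comparison is unbiased in expectation, type I error stays near 0.05, and 128 remains the right total for the stated inputs.

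The size depends on facts that the article does not give. With a few large centres, the imbalance risk is negligible and what remains is a small gain in power. With centres of about 16 children or fewer, uneven splits are likely somewhere, and some centres may struggle to form pairs and teams. The power gain is about 0.02 at an assumed ICC of 0.05 and 0.04 at 0.10, less whatever baseline adjustment already recovers. The change is worth making because it costs almost nothing and its allocation half cannot be made after the children are assigned.

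**What to change.** - **Section 2.4:** state that a separate 1:1 list is generated for each educational centre, in permuted blocks. Do not add age-band strata. If the full protocol already stratifies by centre, say so here.
- **Section 2.8:** add centre to the ANCOVA alongside age and the baseline outcome, so that the analysis reflects how allocation was done.

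The cost is a few more lists from the same software and one degree of freedom per additional centre. No extra children, visits or staff are needed, and N stays at 128.
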